## Abstract

**Background:**

Despite many advantages over facility-based therapies, less than 25 % of prevalent dialysis patients in Ontario are on a home therapy. Interactive health communication applications, web-based packages for patients, have been shown to have a beneficial effect on knowledge, social support, self-efficacy, and behavioral and clinical outcomes but have not been evaluated in patients with chronic kidney disease (CKD). Web-based tools designed for patients with CKD exist but to our knowledge have not been assessed in their ability to influence dialysis modality decision-making.

**Objective:**

To determine if a web-based tool increases utilization of a home-based therapy in patients with CKD starting dialysis.

**Design:**

This is a multi-centered randomized controlled study.

**Setting:**

Participants will be recruited from sites in Canada.

**Participants:**

Two hundred and sixty-four consenting patients with an estimated glomerular filtration rate (eGFR) less than 20 ml/min/1.73 m^2^ who have received modality education will be enrolled in the study.

**Measurements:**

The primary outcome will be the proportion of participants who are on dialysis using a home-based therapy within 3 months of dialysis initiation. Secondary outcomes will include the proportion of patients intending to perform a home-based modality and measures of dialysis knowledge, decision conflict, and social support.

**Methods:**

The between-group differences in frequencies will be expressed as either absolute risk differences and/or by calculating the odds ratio and its associated 95 % confidence interval.

**Conclusions:**

This study will assess whether access to a website dedicated to supporting and promoting home-based dialysis therapies will increase the proportion of patients with CKD who initiate a home-based dialysis therapy.

**Trial registration:**

ClinicalTrials.gov #NCT01403454, registration date: July 21, 2011.

**Electronic supplementary material:**

The online version of this article (doi:10.1186/s40697-016-0120-y) contains supplementary material, which is available to authorized users.

## What was known before

Interactive health communication applications are web-based tools that provide health information, social, decisional, and/or behavioral change support. A web-based tool that promotes the use of a home-based dialysis therapy has not been formally evaluated in patients with advanced chronic kidney disease (CKD).

## What this adds

This study will determine whether a web-based tool designed to promote home-based dialysis will increase its utilization in incident patients.

## Background

In a person-centered care model, patients with advanced chronic kidney disease (CKD) are provided with the necessary tools and information to select the type of dialysis therapy for which they are best suited. Many programs utilize a specially trained nurse to provide modality education to patients with more advanced CKD (i.e., estimated glomerular filtration rate [eGFR] less than 20 ml/min/1.73 m^2^). There are several modality choices for patients approaching end-stage renal disease (ESRD); these include peritoneal dialysis (PD), a home therapy, or hemodialysis (HD), which either can be at home (HHD) or performed in a facility. In Ontario, Canada, the provincial renal agency’s target for the home dialysis prevalence rate is 40 %, in contrast to the current provincial prevalence of 24 % [1].

Home dialysis offers many advantages over facility-based HD for patients. Home dialysis provides patients with scheduling flexibility which is rarely possible in facility-based HD. PD patients in particular have more freedom to travel and usually enjoy a less restrictive diet with respect to potassium than facility-based HD [2, 3]. Most observational studies suggest that home dialysis patients enjoy better scores in many quality of life domains, particularly treatment satisfaction and therapy intrusiveness [4–6], although some studies have not seen such a difference [7–9]. Home-based dialysis is also beneficial from the payer perspective; overall, healthcare costs are reduced by as much as US$20,000 per patient-year [10–12].

Numerous barriers to initiation of home-based therapies have been described, including provider beliefs, practices, and lack of adequate patient and provider education [13]. In addition to these systemic barriers to home dialysis, many barriers exist at the patient level, including lack of self-efficacy and confidence in performing the therapy, burden on family members, and fear of a catastrophic event [14–18]. Information gaps despite education being provided by care providers may lead to increased decisional uncertainty and conflict, particularly in an era when home-based therapies are being more actively encouraged. On the other hand, medical contraindication to a home therapy is uncommon; in one study, only 11 % of patients had a medical contraindication [18].

Interactive health communication applications (IHCAs) are computer-based packages for patients which are usually web-based and in addition to providing health information offer some form of social, decisional, and/or behavioral change support [19]. IHCAs facilitate the transfer of information and enable informed decision-making as well as the promotion of healthy behaviors and choices, peer information exchange and support, and self-care. A systematic review of IHCAs developed for individuals with chronic diseases such as diabetes mellitus (DM) and asthma identified 24 randomized controlled trials involving 3739 participants. IHCAs had a beneficial effect on knowledge, social support, self-efficacy, and behavioral and clinical outcomes [19]. Websites designed for patients with CKD who must make decisions regarding treatment options exist but to our knowledge have not been formally evaluated.

The primary objective therefore of this study is to determine if utilization of a website dedicated to the promotion of home-based dialysis will increase the proportion of patients who initiate dialysis using a home-based modality.

## Methods/design

### Study design and randomization

The study is a multi-centered randomized controlled trial comparing the use of a secured web-based IHCA (website www.independentdialysis.ca) versus usual care in the promotion of home-based dialysis therapies. A participant flow diagram is shown in Fig. 1. Randomization is performed using a computer-generated sequence in variable blocks, stratified by site and allocation occurring using sequentially numbered sealed opaque envelopes. Each study participant will be assigned a unique number. The information about randomization sequence and block size will be kept confidential.

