### Setting

The intervention is currently taking place in three multidisciplinary CKD clinic sites in Ontario. Additional sites will be approached to participate as needed to achieve recruitment objectives. Each of the three sites is an academic regional referral center for patients for nephrology services including management of CKD, dialysis, and renal transplantation patients. There are currently about 2300 patients registered in multidisciplinary CKD clinics across the three sites. The study has been approved at each of the local institutional research ethics boards [Hamilton Integrated Research Ethics Board (HIREB)].

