### Statistical considerations

In all analyses, participants randomized will be analyzed according to the group to which they were allocated. All ratios and differences will be calculated as the experimental group compared to the control group. These analyses may be modified in the final statistical analysis plan at any time prior to the investigators accessing the study data in an unblinded fashion. The between-group differences in frequencies will be expressed as either absolute risk differences and their associated 95 % confidence intervals and/or by calculating the odds ratio and its associated 95 % confidence interval (exact binomial method). The between-group differences in continuous variables between groups will be assessed using repeated measures analyses. Sensitivity analyses will be performed by assessing the treatment effect after adjusting for baseline risk factors of known or highly suspected association with modality choice. These factors will include age, sex, diabetes mellitus status, socioeconomic strata, availability of a caregiver, presence of cognitive impairment (assessed by the Montreal Cognitive Assessment (MoCA) score [22], frailty [23], health literacy [24], and other comorbidities. To avoid model over-fitting, we will include only an appropriate number of variables (no more than one per 12 home-based dialysis events) and include them in the order in which they are written above. A two-sided *p* value of <0.05 will be regarded as significant without adjustment for multiple comparisons. The baseline probability of selecting home-based dialysis is assumed to be 28 % based on local data. Assuming an alpha value of 0.05, and 80 % power to detect a 22 % absolute difference between the intervention and usual care groups in the proportion of participants starting home-based dialysis, it is estimated that 152 participants would need to initiate dialysis to detect a significant difference between groups. Based on analysis of historical local clinic data on transition rates to ESRD therapies, it is anticipated that 264 participants will need to be recruited and followed for at least 1 year to achieve the required number of events. This recruitment target will be re-evaluated periodically and adjusted as needed based on differences between projected and when actual dialysis starts relative to the total number of recruited participants.

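### Randomisation is stratified by site, but no analysis the article describes uses site, and its covariate rule would keep site out of the adjusted models (minor)

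*Protocol article*

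**What the plan says.** Study design and randomization: "Randomization is performed using a computer-generated sequence in variable blocks, stratified by site". Site is the only stratification factor named. Under Setting, "The intervention is currently taking place in three multidisciplinary CKD clinic sites in Ontario", and more sites may be added if recruitment needs them.

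Statistical considerations describes three kinds of analysis:

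- Between-group differences in frequencies are "expressed as either absolute risk differences and their associated 95 % confidence intervals and/or by calculating the odds ratio", the latter by an exact binomial method. No strata are mentioned.
- For the scales, "The between-group differences in continuous variables between groups will be assessed using repeated measures analyses". No site term is mentioned.
- Sensitivity analyses adjust for baseline factors: "These factors will include age, sex, diabetes mellitus status, socioeconomic strata, availability of a caregiver, presence of cognitive impairment", then frailty, health literacy and other comorbidities. The number of variables is limited to "no more than one per 12 home-based dialysis events) and include them in the order in which they are written above".

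The same section allows the final statistical analysis plan, which is not shown, to modify these analyses before unblinded access to the data.

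**The concern.** Blocking within site balances the arms on site. If site predicts the outcome, that balance makes the estimated risk difference more precise than an unstratified standard error shows. The reported interval is then wider than it need be, and the test falls below its nominal level.

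Site could plausibly predict the outcome here. The Background lists provider beliefs and practices among the barriers to home dialysis, and these can vary by centre. The primary outcome also counts participants who never start dialysis as non-home, so site differences in start rate feed into it too.

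For the primary comparison, site is simply not mentioned. For the adjusted models the article goes further: the list is explicit, ordered and capped, so following it as written excludes the one factor the design balanced on. At stake is a small loss of precision and power, and a choice between stratified and unstratified results that should be settled before the data are seen.

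**Working it through.** **Inputs from Statistical considerations:** control rate 28%; difference 22 points, so 50% on intervention; two-sided 0.05; 80% power; 152 dialysis starters; 264 recruited. **Assumed, because the article does not give them:** 1:1 allocation, three equal sites, the same risk difference among starters at each site, and the size of the site differences.

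**1. The plan's own figure.** With pooled variance and no continuity correction, mean rate 0.39:

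n per arm = [1.960·√(2·0.39·0.61) + 0.842·√(0.28·0.72 + 0.50·0.50)]² / 0.22² = 75.97, rounded up to 76, so 152 in total. The stated figure is reproduced, by a formula that ignores site.

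**2. What the covariate cap admits.** Expected home-dialysis events = 76·0.28 + 76·0.50 = 59.28. Then 59.28/12 = 4.94, so four variables enter: age, sex, diabetes and socioeconomic strata. Site is not on the list at any position.

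**3. Risk difference at N = 264.** Non-starters count as non-home and participants are analysed as randomised, so the denominator is everyone randomised. The start fraction is 152/264 = 57.6%. The rates become 0.28·0.576 = 16.1% and 0.50·0.576 = 28.8%.

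- Unstratified variance: (0.1612·0.8388 + 0.2879·0.7121)/132 = 0.002578. The 95% half-width is 1.96·√0.002578 = 9.95 points.
- Stratified variance: with shifts of −s, 0, +s among starters, the between-site variance in each arm is (2/3)(0.576·s)². This drops out of the numerator for both arms. At s = 0.20: (0.3402 − 2·0.00884)/132 = 0.002444, half-width 9.69 points.

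| Site shift among starters | Stratified half-width (points) | Narrower by | Power, unstratified / stratified |
|---|---|---|---|
| 0 | 9.95 | 0% | 70.4% / 70.4% |
| ±5 | 9.93 | 0.2% | 70.4% / 70.5% |
| ±10 | 9.89 | 0.7% | 70.5% / 70.9% |
| ±13 | 9.84 | 1.1% | 70.6% / 71.3% |
| ±20 | 9.69 | 2.6% | 70.9% / 72.7% |

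Power is by Wald approximation. A simulation of 40,000 trials with home rates of 15/28/41% among starters (±13) gave power of 70.4% against 71.0%. Type I error was 4.7% unstratified and 5.1% stratified, with a Monte Carlo error of about √(0.05·0.95/40,000) = 0.1 point.

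**4. If start rates also differ.** Let start rates of 43/58/72% run in the same direction as home rates of 15/28/41%. The same formulas, using the product of start rate and home rate at each site, give half-widths of 10.15 and 9.81 points: 3.4% narrower. Unstratified type I error is then about 4.3%. If the two gradients run in opposite directions they largely cancel, and the narrowing is about 0.2%.

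**5. Odds ratio (152 starters, 28% vs 50%).** Unadjusted log odds ratio: ln[1/(0.28/0.72)] = 0.944, standard error 0.343, z = 2.75. With a common site-conditional odds ratio that keeps the same marginal rates:

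| Site SD (logit) | Conditional log-OR | SE | z |
|---|---|---|---|
| 0.25 | 0.958 | 0.346 | 2.77 |
| 0.50 | 0.999 | 0.355 | 2.82 |
| 0.75 | 1.066 | 0.369 | 2.89 |
| 1.00 | 1.158 | 0.388 | 2.99 |

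Adjusting for site raises the standard error and moves the estimate further from 1. The interval does not narrow; only the test statistic gains.

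**The case against.** The best case against the point is that this is a condensed article. The analysis plan is not shown, and the article expressly allows it to change the analyses. The article names effect measures without calling them unstratified, and either measure could be computed by site. All three sites are described as the same kind of academic referral centre, and no site-specific rates are given, so any harm is hypothetical and at most small.

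Much of this stands. Absence of site can be asserted only of the analyses the article describes. For the primary comparison, silence alone would be weak grounds. What the deferral does not cure is the covariate rule: it is written out, with an order and a cap, and it omits the stratification factor. Permission to change it later is a chance to correct it, not evidence that it has been corrected.

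A reader might infer that the primary confidence interval is too wide as a matter of fact. The documents do not support that: it depends on site differences they do not report, and the effect vanishes if sites are alike. A reader might also extend the claim to the odds ratio. That is wrong, because site adjustment there widens the log-scale interval and changes what is estimated. Nor does adding sites necessarily make the loss grow, since new sites need not increase between-site variation.

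**Conclusion.** The point holds as a minor one. The design stratifies on site, no described analysis uses it, and the covariate rule as written keeps it out of the adjusted models.

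For the risk difference the consequence is slight conservatism: the interval could be 0% to 2.6% narrower over the assumed range of site shifts (about a quarter of a percentage point of half-width at the extreme), and 3.4% narrower in the illustrated case where start rates rise with home uptake. Power lost is at most about 2 points over the range tabulated. The risk difference is not biased, type I error is not inflated, and the figure of 152 is unaffected.

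These sizes rest on three equal sites, 1:1 allocation and the assumed site differences.

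**What to change.** State in the analysis plan, before unblinded access to the data:

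- The primary comparison is a Mantel-Haenszel risk difference stratified by site, with its 95% confidence interval.
- If an odds ratio is reported, it is a site-stratified exact odds ratio, described as site-conditional, with a note that stratification helps the test rather than narrowing the interval.
- Site is in every adjusted model, outside the ordered list and not counted against the one-per-12 limit.

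The cost is a few sentences. It needs no extra data, because site is already recorded for randomisation, and no change to the sample size.

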**Fig. 1 Fig1:**
[figure not shown]
Flow of participants in the study

### Setting

The intervention is currently taking place in three multidisciplinary CKD clinic sites in Ontario. Additional sites will be approached to participate as needed to achieve recruitment objectives. Each of the three sites is an academic regional referral center for patients for nephrology services including management of CKD, dialysis, and renal transplantation patients. There are currently about 2300 patients registered in multidisciplinary CKD clinics across the three sites. The study has been approved at each of the local institutional research ethics boards [Hamilton Integrated Research Ethics Board (HIREB)].

### Participants

All eligible participants are identified by the local CKD clinic electronic database and screened for eligibility by CKD nurses in the circle of care. All eligible participants are then approached and asked if they are interested in speaking to research staff about the study. Consented participants are then randomized into one of two study arms: (1) usual care or (2) the IHCA. The participant inclusion and exclusion criteria are shown in Table 1.

**Table 1 Tab1:** Patient inclusion and exclusion criteria

Inclusion criteria	Exclusion criteria
1. Age ≥18 years 2. Enrolled in CKD clinic 3. Previously received ESRD modality education 4. Personal access to a home computer with Internet access 5. Most recent eGFR ≤20 ml/min/1.73 m^2^ 6. Declared intent for either dialysis or transplant	1. Absolute medical contraindication to home-based dialysis 2. Inability to provide informed consent 3. Inability to use a home computer and Internet 4. Inability to understand English (written and spoken) 5. Severe visual or auditory impairment

Abbreviations: *CKD* chronic kidney disease, *ESRD* end-stage renal disease, *eGFR* estimated glomerular filtration rate, *ml* milliliters, *min* minutes, and *m*
^*2*^ meter squared

### Intervention

Participants in both the usual care and IHCA arms continue to be seen in the CKD clinic as part of usual care. Participants randomized to the IHCA arm will be logged in to the website during the randomization visit and provided an orientation session to familiarize them with the website. They are asked to generate their own password and encouraged to log on to the website regularly. Email reminders to log-in are sent periodically and the frequency of participants’ visits monitored. The website was developed with a view to ensure easy navigation for participants, while providing content that encompasses informational and social support to reduce conflict and uncertainty in ESRD therapy decision-making. The informational support component of the website includes a section for *Frequently Asked Questions*, demonstration videos, and still photographs of equipment, as well as pre-recorded video interviews with local experts and existing patients. Updated information will continue to be added by a variety of content-expert healthcare professionals as it comes available. The social support component of the website will include video and text narratives of patients addressing the benefits and challenges of home dialysis, and a moderated forum for participants to discuss issues surrounding home dialysis with current home dialysis patients. Participants will also have the opportunity to email “experts,” including nephrologists, nurses, and existing home dialysis patients with any questions they may have. The available resources are available to all participants randomized to the intervention group, regardless of their intended modality.

### Outcomes

The primary outcome is the proportion of participants who receive any dialysis using a home-based therapy (PD or HHD) within 3 months of dialysis initiation. Participants that do not start dialysis or who receive a pre-emptive transplantation at study close will be regarded as non-home-based dialysis outcomes. Participants for which a modality cannot be ascertained will be considered non-home dialysis outcomes. Secondary outcomes include (1) proportion of patients intending to perform a home-based dialysis at 1 year, (2) dialysis knowledge as measured using a locally developed assessment tool (available online as Additional file 1), (3) decision conflict measured using the Decisional Conflict Scale [20], and (4) level of social support measured with the Duke-UNC Functional Social Support Questionnaire [21]. All of the above outcomes will be measured at baseline and 6 and 12 months post intervention.

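### Baseline intention is collected but used in no stated analysis, so the main comparison of 1-year intention to do home dialysis is valid but less precise than it could be

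*Protocol article*

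**What the plan says.** The Outcomes section of the Protocol article lists as its first secondary outcome the "proportion of patients intending to perform a home-based dialysis at 1 year". It then gives the schedule: "All of the above outcomes will be measured at baseline and 6 and 12 months post intervention".

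Statistical considerations assigns methods by type of variable.

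- For proportions: "The between-group differences in frequencies will be expressed as either absolute risk differences and their associated 95 % confidence intervals". An odds ratio may be given as well or instead. The interval method named in the same sentence is the "exact binomial method", which is an unadjusted two-group method.
- For continuous outcomes: "The between-group differences in continuous variables between groups will be assessed using repeated measures analyses".
- For covariate adjustment: "Sensitivity analyses will be performed by assessing the treatment effect after adjusting for baseline risk factors of known or highly suspected association with modality choice". The list begins: "These factors will include age, sex, diabetes mellitus status, socioeconomic strata, availability of a caregiver, presence of cognitive impairment". It continues with frailty, health literacy and other comorbidities. Intention at baseline is not on it. The number of covariates is capped at one per 12 home-dialysis events.

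The same section allows the final analysis plan to change these analyses until the investigators have unblinded access to the data.

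**The concern.** Intention is binary, so by the stated rule its main analysis sets the 1-year proportions of the two arms side by side. The participant's own answer at entry is not used there, nor in the sensitivity analyses. Yet a person's earlier answer to the same question is plausibly among the best predictors of the later one. Table 1 requires that all participants have already had modality education, and the Intervention section refers to the modality they intend, so many may hold a preference at entry.

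What is at stake is the width of the interval for an outcome close to the website's purpose. The Discussion describes the website as meant to support the decision to choose a home modality. Intention measures that decision directly, including in people who never start dialysis during the study and whom the primary outcome counts as not on home dialysis.

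**Working it through.** **The plan's own figure.** The only calculation in the document is for the primary outcome: 28% versus 50%, two-sided alpha 0.05, 80% power. With the pooled-variance formula and p̄ = 0.39:

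n per arm = [1.960·√(2·0.39·0.61) + 0.842·√(0.28·0.72 + 0.50·0.50)]² / 0.22² = (1.352 + 0.566)² / 0.0484 ≈ 76, so 152 in total.

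This reproduces the stated 152 and is unaffected by the present point. No figure is given for the intention outcome.

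**Inputs for the intention outcome.**

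- 264 participants: from the document.
- 132 per arm: assumes 1:1 allocation (the ratio is not stated) and that everyone is measured at 12 months.
- 28% intending home dialysis at baseline, and in the control arm at 1 year: assumed, borrowed from the planning rate for the primary outcome.
- 40% in the website arm at 1 year: assumed.
- Correlation r between baseline and 1-year intention: not in the document, taken as 0.3, 0.5 and 0.7.

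**Crude comparison.** SE = √[(0.28·0.72 + 0.40·0.60)/132] = √(0.4416/132) = 5.8 points. The 95% half-width is 1.96 × 5.8 = 11.3 points. Power ≈ Φ(0.12/0.0578 − 1.96) = Φ(0.115) ≈ 54 to 55%.

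**Adjusted for baseline intention.** On the risk-difference scale, SE(adjusted) ≈ SE(crude)·√(1 − r²). The equivalent crude sample size is 132/(1 − r²) per arm.

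| r | √(1 − r²) | SE (points) | Half-width (points) | Narrowing | Power | Equivalent crude n per arm |
|---|---|---|---|---|---|---|
| none (crude) | 1 | 5.8 | 11.3 | – | 54–55% | 132 |
| 0.3 | 0.954 | 5.5 | 10.8 | 5% | 58% | 145 |
| 0.5 | 0.866 | 5.0 | 9.8 | 13% | 67% | 176 |
| 0.7 | 0.714 | 4.1 | 8.1 | 29% | 83% | 259 |

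A simulation of 20,000 trials per setting, with linear adjustment for baseline and robust standard errors, gave reductions of 4%, 13% and 28% and power of 0.585, 0.666 and 0.828. The proportional narrowing does not depend on the number of participants.

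**Other assumed rates.** With 40% versus 55% at 132 per arm, power is 69% crude and 74%, 81% and 93% adjusted at the same three correlations. The pattern is the same.

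**How large r can be.** In the website arm, with 28% at baseline and 40% at 1 year, r cannot exceed √[(0.28·0.60)/(0.72·0.40)] = 0.76. The share of baseline home-intenders in that arm who still intend home dialysis at 1 year is [0.28·0.40 + r·√(0.28·0.72·0.40·0.60)]/0.28. That is 64%, 79% and 95% at r = 0.3, 0.5 and 0.7. The last value is therefore close to a ceiling.

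**Chance baseline imbalance.** The SD of the difference between arms in baseline intention is √(2·0.28·0.72/132) = 5.5 points. The part of the crude standard error that comes from baseline intention is r × 5.8 points: 2.9 at r = 0.5 and 4.0 at r = 0.7. At r = 0.5, √(2.9² + 5.0²) = 5.8, which is the crude standard error again. Chance imbalance is thus already inside the crude interval; it is the same quantity as the precision loss.

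**Bias.** In simulation at 40% versus 55%, the crude estimate averaged 14.9 to 15.1 points against a true 15.

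**The case against.** The strongest reply is that nothing here is wrong. A risk difference or odds ratio with a 95% interval is a valid comparison of randomised proportions, and the covariates of a secondary analysis are often left to the analysis plan, which the protocol says may still change these analyses. The first part stands: this is lost efficiency, not an error or a contradiction. The second stands only in part. The protocol is not silent: it assigns a method to each type of variable and names the adjustment factors, and baseline intention is in neither place. The freedom to modify shows that the change is still open; it does not alter what is now specified.

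A reader might infer several stronger points that the documents do not support.

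- *That chance imbalance biases the estimate or is a second harm.* Randomisation keeps the crude contrast unbiased, and its interval already allows for such imbalance.
- *That intention is compared only crudely.* The adjusted sensitivity analyses are not expressly limited to the primary outcome, although the cap on home-dialysis events points there. They omit baseline intention, so they do not recover the lost precision.
- *That 1-year intention must follow baseline closely.* No passage says so. Table 1 requires a declared intent for dialysis or transplant, not for home versus facility, and the Background describes decisional uncertainty. Strong tracking is an assumption.
- *That the lack of a repeated-measures model is itself the loss.* The figures above come from baseline adjustment alone. The gain from the 6-month values was not quantified, and the article states no missing-data rule from which to conclude that people without a 12-month answer are dropped.

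**Conclusion.** The point holds as a minor efficiency weakness in one secondary outcome. The trial collects baseline intention, and no stated analysis uses it. The stated comparison remains valid and unbiased.

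The cost depends on a correlation that the document does not give. Under the assumptions shown, the interval is wider than it need be by an amount that adjustment would cut by about 5% at r = 0.3, which is little, 13% at r = 0.5, and 29% at r = 0.7, which is near the limit and should not be read as the expected case. The power figures are illustrations: the trial claims no power for this outcome. The primary outcome and its sample size are untouched.

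**What to change.** In Statistical considerations, or in the final analysis plan before unblinded access, state that the main analysis of 1-year intention is a binary regression with arm and baseline intention as terms. Report a standardised risk difference with 95% interval alongside the odds ratio, and keep the crude proportions by arm as description.

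As an optional extension, a GEE or mixed logistic model could add the 6-month values, with the 12-month contrast as the estimate. If this is chosen, the plan must first say how intention is handled for participants already on dialysis at a visit; otherwise the model would implicitly fill in an intention for them.

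The cost is a sentence or two of plan wording and a standard model, with no new data, visits or participants. The one small downside is that the adjusted odds ratio is conditional on baseline intention and so is not directly comparable with the crude one. That is why the standardised risk difference should stand beside it.
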